# Efficacy and Safety of Electro-Thumbtack Needle Therapy for Patients With Chronic Neck Pain: Protocol for a Randomized, Sham-Controlled Trial

**DOI:** 10.3389/fmed.2022.872362

**Published:** 2022-04-29

**Keywords:** acupuncture, chronic neck pain, RCT, electro-thumbtack needle, efficacy and safety

## Abstract

**Background:**

Chronic neck pain is a prevalent condition adversely impacting patients' wellbeing in both life and work experience. Electro-thumbtack needle (ETN) therapy, combining acupuncture with transcutaneous stimulation, might be one of the effective complementary and alternative medicine (CAM) therapies in treating chronic neck pain, although the evidence is scarce. This study aims to estimate the efficacy and safety of ETN therapy for chronic neck pain.

**Methods and Analysis:**

This is a sham-controlled, randomized clinical trial. A total of 180 subjects will be randomly allocated to either the ETN group or the sham ETN group. Treatment will be administrated three times a week for four consecutive weeks, with a 6-month follow-up. The primary outcome measure will be the Numerical Rating Scale for neck pain (NRS-NP) over a period of the 4 weeks. Secondary outcome measures include the Northwick Park Neck Pain Questionnaire (NPQ), Neck Disability Index (NDI), Patient Global Impression of Change (PGIC), patient expectation, and preference assessment. The chi-square test or Fisher's exact test will be used for proportions of participants having clinically meaningful improvement. Analysis of covariance or repeated-measures analysis of variance will be applied to examine changes in the outcome measures from baseline.

**Discussions:**

This prospective trial will contribute to evaluating the efficacy and safety of ETN in the treatment of chronic neck pain, with an intermediate-term follow-up. This study will provide further evidence for clinical neck pain management.

**Ethics and Dissemination:**

This trial has been approved by the Research Ethical Committee of Guang'anmen Hospital (ethical approval number: 2021-039-KY-01). Recruitment began in March 2022 and will continue until December 2023. Dissemination plans include posters, WeChat, websites, and bulletin boards in hospital and communities.

**Clinical Trial Registration:**

This trial is registered at ClinicalTrials.gov (identifier: NCT04981171).

## Introduction

Chronic neck pain is a common physical complaint across the world and the fourth leading impairment in terms of years lived with disability (1, 2). Its lifetime prevalence is around 48.5% (3). Neck pain is mainly due to poor posture or anxiety, especially in women and the middle-aged population (4). Previous clinical trials have demonstrated that therapies including exercise, acupuncture, and transcutaneous electrical nerve stimulation (TENS) have moderate effects in pain alleviation (5–8). However, management of chronic neck pain remains complex and challenging.

Acupuncture has been widely used for pain alleviating around the world. In previous studies, acupuncture or electroacupuncture is more effective than sham controls (6, 8–11). Clarified evidence supported that acupuncture could produce opioids and other bioactive antalgic chemicals (12). It is thus recommended for the treatment of chronic neck pain by consensus (6, 8, 13). Nevertheless, the application of acupuncture is limited to a large extent due to the patients' fright of and intolerance to needling pain. TENS, a non-invasive physical therapy, is more popular and comfortable. Evidence from clinical trials supported the effectiveness of TENS for chronic neck pain (14–16). The pain could be alleviated *via* stimulation either on acupoints or trigger points, both immediately after treatment and during follow-up periods (15, 17, 18). However, the difference between TENS and sham control is not significant, especially at the long-term follow-ups (14, 18).

A combination of acupuncture with conservational treatment, such as TENS, is considered to benefit the patients more in comparison with single therapy (8, 13). The emergence of electro-thumbtack needle (ETN) therapy is in response to this recommendation, aiming to achieve better effectiveness while maintaining comfortable. The device of ETN is composed of a thumbtack needle with 2 mm long body and a small rechargeable and portable electric stimulator, which outputs current. The surface of thumbtack needle is modified with conductive material to reinforce electric stimulation on acupoints. It is a convenient therapy that can be easily operated by patients on their own after training. In light of the good effectiveness of acupuncture and TENS published in previous studies, as well as the convenience of ETN, we plan to conduct this study to estimate the efficacy and safety of ETN therapy for chronic neck pain in comparison with sham ETN therapy.

## Methods and Analysis

### Study Design

This study is a single-center, participant-blinded, randomized controlled trial, which will be conducted from March 2022 to December 2023 in Guang'anmen Hospital, China Academy of Chinese Medical Sciences. The study flowchart is shown in Figure 1. We design this protocol conforming to the guidelines of the Standard Protocol Items: Recommendations for Interventional Trials (SPIRIT) (19) (Table 1) and the Consolidated Standards of Reporting Trials (CONSORT). This trial has been approved by the Institutional Review Board of Guang'anmen Hospital, China Academy of Chinese Medical Sciences (ethical approval number: 2021-039-KY-01), and it has been registered at ClinicalTrials.gov on July 18, 2021 (Identifier: NCT04981171). Each participant will receive 4-week treatment and will be followed up for 6 months.

**Figure 1 F1:**
[figure not shown]
Study flowchart. ETN, electro-thumbtack needle; NRS-NP, numerical rating scale for neck pain; NPQ, the northwick park neck pain questionnaire; NDI, neck disability index; PGIC, patient global impression of change.

**Table 1 T1:** SPIRIT 2013 checklist: recommended items to address in a clinical trial protocol and related documents^*^.

**Section/item**	**Item no**	**Description**	**Yes/No**
**Administrative information**			
Title	1	Descriptive title identifying the study design, population, interventions, and if applicable, trial acronym	Yes
Trial registration	2a	Trial identifier and registry name. If not yet registered, name of intended registry	Yes
	2b	All items from the World Health Organization Trial Registration Data Set	Yes
Protocol version	3	Date and version identifier	Yes
Funding	4	Sources and types of financial, material, and other support	Yes
Roles and responsibilities	5a	Names, affiliations, and roles of protocol contributors	Yes
	5b	Name and contact information for the trial sponsor	Yes
	5c	Role of study sponsor and funders, if any, in study design; collection, management, analysis, and interpretation of data; writing of the report; and the decision to submit the report for publication, including whether they will have ultimate authority over any of these activities	Yes
	5d	Composition, roles, and responsibilities of the coordinating center, steering committee, endpoint adjudication committee, data management team, and other individuals or groups overseeing the trial, if applicable (see Item 21a for data monitoring committee)	Yes
**Introduction**			
Background and rationale	6a	Description of research question and justification for undertaking the trial, including summary of relevant studies (published and unpublished) examining benefits and harms for each intervention	Yes
	6b	Explanation for choice of comparators	Yes
Objectives	7	Specific objectives or hypotheses	Yes
Trial design	8	Description of trial design including type of trial (e.g., parallel group, crossover, factorial, single group), allocation ratio, and framework (e.g., superiority, equivalence, non-inferiority, exploratory)	Yes
**Methods: participants, interventions, and outcomes**			
Study setting	9	Description of study settings (e.g., community clinic, academic hospital) and list of countries where data will be collected. Reference to where list of study sites can be obtained	Yes
Eligibility criteria	10	Inclusion and exclusion criteria for participants. If applicable, eligibility criteria for study centers and individuals who will perform the interventions (e.g., surgeons, psychotherapists)	Yes
Interventions	11a	Interventions for each group with sufficient detail to allow replication, including how and when they will be administered	Yes
Interventions: modifications	11b	Criteria for discontinuing or modifying allocated interventions for a given trial participant (e.g., drug dose change in response to harms, participant request, or improving/worsening disease)	Yes
Interventions: adherence	11c	Strategies to improve adherence to intervention protocols, and any procedures for monitoring adherence (e.g., drug tablet return; laboratory tests)	Yes
Interventions: concomitant care	11d	Relevant concomitant care and interventions that are permitted or prohibited during the trial	Yes
Outcomes	12	Primary, secondary, and other outcomes, including the specific measurement variable (e.g., systolic blood pressure), analysis metric (e.g., change from baseline, final value, time to event), method of aggregation (e.g., median, proportion), and time point for each outcome. Explanation of the clinical relevance of chosen efficacy and harm outcomes is strongly recommended	Yes
Participant timeline	13	Time schedule of enrolment, interventions (including any run-ins and washouts), assessments, and visits for participants. A schematic diagram is highly recommended (see Figure 1)	Yes
Sample size	14	Estimated number of participants needed to achieve study objectives and how it was determined, including clinical and statistical assumptions supporting any sample size calculations	Yes
Recruitment	15	Strategies for achieving adequate participant enrolment to reach target sample size	Yes
**Methods: assignment of interventions (for controlled trials)**			
Allocation:			
Sequence generation	16a	Method of generating the allocation sequence (e.g., computer-generated random numbers), and list of any factors for stratification. To reduce predictability of a random sequence, details of any planned restriction (e.g., blocking) should be provided in a separate document that is unavailable to those who enroll participants or assign interventions	Yes
Allocation concealment mechanism	16b	Mechanism of implementing the allocation sequence (e.g., central telephone; sequentially numbered, opaque, sealed envelopes), describing any steps to conceal the sequence until interventions are assigned	Yes
Implementation	16c	Who will generate the allocation sequence, who will enroll participants, and who will assign participants to interventions	Yes
Blinding (masking)	17a	Who will be blinded after assignment to interventions (e.g., trial participants, care providers, outcome assessors, data analysts), and how	Yes
	17b	If blinded, circumstances under which unblinding is permissible, and procedure for revealing a participant's allocated intervention during the trial	Yes
**Methods: data collection, management, and analysis**			
Data collection methods	18a	Plans for assessment and collection of outcome, baseline, and other trial data, including any related processes to promote data quality (e.g., duplicate measurements, training of assessors) and a description of study instruments (e.g., questionnaires, laboratory tests) along with their reliability and validity, if known. Reference to where data collection forms can be found, if not in the protocol	Yes
	18b	Plans to promote participant retention and complete follow-up, including list of any outcome data to be collected for participants who discontinue or deviate from intervention protocols	Yes
Data management	19	Plans for data entry, coding, security, and storage, including any related processes to promote data quality (e.g., double data entry; range checks for data values). Reference to where details of data management procedures can be found, if not in the protocol	Yes
Statistical methods	20a	Statistical methods for analyzing primary and secondary outcomes. Reference to where other details of the statistical analysis plan can be found, if not in the protocol	Yes
	20b	Methods for any additional analyses (e.g., subgroup and adjusted analyses)	No
	20c	Definition of analysis population relating to protocol non-adherence (e.g., as randomized analysis), and any statistical methods to handle missing data (e.g., multiple imputation)	Yes
**Methods: monitoring**			
Data monitoring	21a	Composition of data monitoring committee (DMC); summary of its role and reporting structure; statement of whether it is independent from the sponsor and competing interests; and reference to where further details about its charter can be found, if not in the protocol. Alternatively, an explanation of why a DMC is not needed	Yes
	21b	Description of any interim analyses and stopping guidelines, including who will have access to these interim results and make the final decision to terminate the trial	Yes
Harms	22	Plans for collecting, assessing, reporting, and managing solicited and spontaneously reported adverse events and other unintended effects of trial interventions or trial conduct	Yes
Auditing	23	Frequency and procedures for auditing trial conduct, if any, and whether the process will be independent from investigators and the sponsor	Yes
**Ethics and dissemination**			
Research ethics approval	24	Plans for seeking research ethics committee/institutional review board (REC/IRB) approval	Yes
Protocol amendments	25	Plans for communicating important protocol modifications (e.g., changes to eligibility criteria, outcomes, analyses) to relevant parties (e.g., investigators, REC/IRBs, trial participants, trial registries, journals, regulators)	Yes
Consent or assent	26a	Who will obtain informed consent or assent from potential trial participants or authorized surrogates, and how (see Item 32)	Yes
	26b	Additional consent provisions for collection and use of participant data and biological specimens in ancillary studies, if applicable	No
Confidentiality	27	How personal information about potential and enrolled participants will be collected, shared, and maintained in order to protect confidentiality before, during, and after the trial	Yes
Declaration of interests	28	Financial and other competing interests for principal investigators for the overall trial and each study site	Yes
Access to data	29	Statement of who will have access to the final trial dataset, and disclosure of contractual agreements that limit such access for investigators	Yes
Ancillary and post-trial care	30	Provisions, if any, for ancillary and post-trial care, and for compensation to those who suffer harm from trial participation	Yes
Dissemination policy	31a	Plans for investigators and sponsor to communicate trial results to participants, healthcare professionals, the public, and other relevant groups (e.g., *via* publication, reporting in results databases, or other data sharing arrangements), including any publication restrictions	Yes
	31b	Authorship eligibility guidelines and any intended use of professional writers	Yes
	31c	Plans, if any, for granting public access to the full protocol, participant-level dataset, and statistical code	No
**Appendices**			
Informed consent materials	32	Model consent form and other related documentation given to participants and authorized surrogates	Yes
Biological specimens	33	Plans for collection, laboratory evaluation, and storage of biological specimens for genetic or molecular analysis in the current trial and for future use in ancillary studies, if applicable	No

* *It is strongly recommended that this checklist be read in conjunction with the SPIRIT 2013 Explanation & Elaboration for important clarification on the items. Amendments to the protocol should be tracked and dated. The SPIRIT checklist is copyrighted by the SPIRIT Group under the Creative Commons “Attribution-NonCommercial-NoDerivs 3.0 Unported” license*.

### Eligibility Criteria

#### Inclusion Criteria

Participants conforming to the following criteria are included:

Neck pain accompanied with headaches or movement coordination impairments according to the Orthopedic Section of the American Physical Therapy Association (APTA) (7);Aged 18–65 years;History of neck pain for at least 3 months;Scoring at least 4 on Numerical Rating Scale for Neck Pain (NRS-NP) assessing the average neck pain intensity over the last 7 days (12, 20–23).

#### Exclusion Criteria

Participants who meet any of the following criteria are excluded:

Neck pain with mobility deficits or radiating neck pain according to the Orthopedic Section, APTA (7);Neck pain secondary to specific diseases, such as tumor, immune disease, endocrine and metabolic disorders, neurological abnormalities, cervical vertebra fracture, and cervical dislocation;Acute or radiating neck pain or pain accompanied with upper limb symptoms;Neck pain with sensory or motor disturbance;Prior cervical spine surgery or congenital abnormalities;Experiencing medical dispute litigation;With the experience of acupuncture in the past 30 days;In the administration of analgesic, muscle relaxant, hormones, or having greater pain in other regions of the body;Allergic to metal or the adhesive tape, implantation of cardiac pacemaker, or ulceration of skin at selected acupoints;Disable to communicate or critically ill;Drug or alcohol dependent;Currently or planning to be pregnant.

### Recruitment

A total of 180 participants with chronic neck pain will be recruited in Guang'anmen Hospital *via* posters, WeChat, websites, and bulletin boards in hospital and communities. Diagnosis will be made by an orthopedist. Eligible participants will be officially enrolled only after signing a written informed consent, and all participants have the right to withdraw their consent later at any time.

### Randomization and Allocation

Eligible participants will be randomly assigned in a 1:1 ratio to either the ETN group or the sham ETN group. The randomization sequence will be generated using a fixed block size by an independent investigator through the SAS 9.4 (SAS Institute, Cary, NC, USA). The randomization number will be sealed in opaque and sequentially labeled envelopes, with the name of the investigator and the date signed over the seals. The envelop will be opened sequentially after the enrollment of participant, and the group allocation will be only informed to the acupuncturist before treatment.

### Blinding

In this trial, the participants, outcome assessors, and the statisticians will all be blinded. The sham ETN was designed to mimic true ETN: the sham thumbtack needle is 0.2 mm long with a blunt tip (instead of a sharp tip), and the electric stimulation is minimal and transient. They will produce a similar sensation of tingling as true ETN, which makes it hard for participants to distinguish. To avoid conversation between groups, participants will be treated separately on alternate days by appointments. After either session in the last week of treatment, blinding assessment will be completed by all participants. They will be told before group allocation: you may be randomly allocated to either the ETN group or the sham ETN group; the electric stimulation is weak in both groups, and you may even be incapable to sense it during the process out of body adaption. Participants will be asked “Which therapy do you think was provided to you?” The available answers include “ETN therapy,” “sham ETN therapy,” or “unclear.”

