**Figure 3 F3:**
[figure not shown]
Electric stimulation device and gel electrode.

Participants will receive three 30-min treatment sessions per week (ideally every other day) for 4 consecutive weeks after baseline assessment.

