#### Safety Assessment

Acupuncture-associated side effects such as bruising, dizziness, nausea, hematomas, infection, palpitations, or severe pricking pain [visual analog score (VAS) ≥ 4], and all other adverse events (AEs) irrelevant to acupuncture, will be carefully observed and recorded. Serious AEs (SAEs) will be reported to the Medical Ethics Committee of Guang'anmen Hospital within 24 h. After each session, the acupuncturist and outcome assessors will document adverse events and side effects if happens.

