## Discussion

The objective of this study is to evaluate the efficacy and safety of ETN therapy for non-specific chronic neck pain. Demographic characteristics will be collected including age, duration, job, psychosocial or physical risk factors, level of exercise, history of injury, and history of autoimmune disease. The outcomes are designed in accordance with the Initiative on Methods, Measurement, and Pain Assessment in Clinical Trials (IMMPACT) recommendations for core outcomes of chronic pain (41). Both the reduction of 30 and 50% on NRS are applied as outcome measures in this trial. Although the reduction of 30% from baseline in NRS is consistently acknowledged as MCID in current studies (15, 23, 25, 27, 28), a 50% reduction is widely used in clinical trials as a rigorous outcome measurement interpreting more significant improvement in symptoms (15, 28, 29). Additionally, multiple outcomes will be evaluated, as various as pain intensity, disability, quality of life, and the degree of subjective satisfaction.

The effectiveness of both manual acupuncture and TENS has been identified by previous studies (15, 42) in reducing chronic neck pain. Since ETN treatment has been an integration of thumbtack needling and electric stimulation, the treatment effect will probably be stronger and comprehensive. Notably, it is easy to administrate thumbtack needles on acupoints, even by patients themselves at home.

In this trial, blunt-tip thumbtack needle with no penetration and transient minimal electric stimulation is designed as sham control. It can produce acupuncture-like sensation of tingling or pain by pressing the blunt tip on acupoints without skin penetrating, similar to the validated placebo needle (43, 44). To maintain the success of blindness, participants from different groups will be avoided to contact with each other. The outcome assessor and the statistician will also be concealed to group allocation. These approaches are constructed to reduce possible biases attached to the results.

Limitations of this study are as follows. Group allocation will be not blinded to the acupuncturist, whose attitude for or against an intervention might be inevitably transferred to participants. Besides, this study does not implement a waitlist control in consideration of ethics principles, in which condition we cannot exclude the influence of spontaneous remission of disease.

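### Separating the groups by treatment day links everyone in one arm through the calendar, which weakens assessor blinding and, with fixed blocks, could make some allocations predictable

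*Protocol article*

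**What the plan says.** The Blinding section of the protocol article sets out who is masked: "In this trial, the participants, outcome assessors, and the statisticians will all be blinded". It then gives the separation rule: "To avoid conversation between groups, participants will be treated separately on alternate days by appointments". The Discussion repeats the aim without mentioning days: "To maintain the success of blindness, participants from different groups will be avoided to contact with each other".

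Session spacing is set elsewhere, under Interventions (ETN Group): "Participants will receive three 30-min treatment sessions per week (ideally every other day) for 4 consecutive weeks after baseline assessment".

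Safety Assessment brings the assessors into contact with treatment days: "After each session, the acupuncturist and outcome assessors will document adverse events and side effects if happens". The events to be recorded there include bruising, hematomas and infection.

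Randomization and Allocation states: "The randomization sequence will be generated using a fixed block size by an independent investigator through the SAS 9.4". The ratio is 1:1. Allocations sit in sealed, opaque, numbered envelopes that are opened in order after enrollment, and only the acupuncturist is told the group. Study Design describes a single center. The block size is not given.

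**The concern.** A rule that keeps the groups apart by day protects participants from comparing notes, but it makes the calendar informative. Without it, a clue about treatment seen in one participant says something about that participant only. With it, the same clue carries over to everyone who attends on the same days.

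Two safeguards are exposed. The first is assessor blinding, because the assessors see participants after sessions and so learn their treatment days. The second is allocation concealment. The calendar sorts past participants into two sets, and fixed 1:1 blocks let anyone who knows that sorting and the block size work out the end of each block before the envelope is opened. Foreknowledge at enrollment can bias who is entered, whoever rates the outcome. The Discussion already concedes that the acupuncturist is unblinded, so the remaining safeguards carry more weight.

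**Working it through.** **1. Does the rule split days by group?** The text allows two readings: each participant comes every other day, or each group has its own days. The stated purpose is to prevent conversation between groups, and the spacing of one participant's sessions is fixed separately under Interventions. Alternate days serve the stated purpose only if the day depends on the group. The split by group is therefore the likelier reading, but it is an inference.

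**2. What does the day reveal to an assessor?** On its own, it reveals who shares a group, not which group is active. A further clue is needed. The ETN needle is 2 mm long and enters the skin, while the sham is 0.2 mm, blunt and stays on the surface. A bruise or hematoma recorded after a session would suggest the ETN arm without proving it. Because the day links participants, that suggestion would extend to the rest of that day's schedule.

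**3. How far could this reach the outcome?** Under Primary Outcome and Measurement, the participant circles the pain score. What remains open to assessor influence is verbal delivery of the scale (mentioned there), follow-up by telephone, data entry by the assessor (both under Data Management and Quality Control) and adverse event recording.

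**4. Predictability of allocations.** The article states no figure on this point, so there is none to reproduce.

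Inputs: ratio 1:1, fixed blocks and one center (article); N = 180 (Recruitment). Assumptions: block size 4, 6 or 8; the person enrolling knows the block size and every earlier allocation in the block.

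In a block of 2k with k places per arm, an allocation is certain once the other arm's places are used up. The certain allocations are the run of identical assignments that ends the block. For either arm, the k assignments of the other arm create k + 1 gaps, so the expected number in the last gap is k/(k + 1). Adding the two arms:

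- expected certain allocations per block = 2k/(k + 1)
- share = [2k/(k + 1)]/(2k) = 1/(k + 1)

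Check for size 4: the six possible orders have final runs of 2, 1, 1, 2, 1 and 1. The mean is 8/6 = 1.333, and 1.333/4 = 1/3.

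| Assumed block size | k | Certain per block | Share certain | Of 180 | Correct if guessing the arm with more places left |
|---|---|---|---|---|---|
| 4 | 2 | 1.333 | 1/3 | 60 | 70.8% |
| 6 | 3 | 1.5 | 1/4 | 45 | 68.3% |
| 8 | 4 | 1.6 | 1/5 | 36 | 66.6% |

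The last column comes from enumerating all orders of a block; intact concealment gives 50%. For size 4 by hand: (0.5 + 0.667 + 0.667 + 1)/4 = 0.708. Since 180 is not a multiple of 8, the 36 is the share applied to 180; 22 full blocks alone give 22 × 1.6 = 35.2. Over a wider range, size 2 gives 1/2 (90 of 180) and size 10 gives 1/6 (30 of 180).

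The calendar alone predicts only which set of days the next person will join. Naming the arm also needs the kind of clue described in step 2.

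**The case against.** The scheduling sentence gives no explicit group-to-day rule, and it may partly restate the every-other-day spacing, which is itself only an ideal. The Discussion speaks of avoiding contact, not of days. The primary score is marked by the participant, so participant blinding matters most, and the separation rule serves exactly that. On concealment, the envelopes are opaque, sealed and opened only after enrollment. The article does not say who enrolls or who books, and the SPIRIT table marks as met the item that calls for blocking details to be kept from enrolling staff. A condensed article may also leave calendar access to the full protocol.

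Most of this stands as a limit on size. It does not remove the point, because the scheduling rule and the fixed block size are stated choices, not omissions, and sealed envelopes do not stop inference from past allocations.

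A reader might infer more than the text supports:

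- **That the day gives away the group at all 180 × 12 = 2,160 planned sessions.** This would need a certain group-to-day rule and perfect adherence to the schedule. The article gives neither.
- **That assessors would see the sham device switched off after 30 s.** The acupuncturist does this during the session, and nothing places assessors in the room.
- **That treatment is confounded with weekday in a way that biases results.** The article gives no clinic days and no mechanism, and the score averages the last 3 days.

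**Conclusion.** The concern holds in a limited form. On the likelier reading, calendar day links all participants of one arm, and assessors who are meant to be blinded learn those days while recording adverse events. One suggestive finding could then point to the arm of a whole day's schedule. This weakens assessor blinding. To say that it defeats it would go too far, because the day does not name the arm and the clue may be ambiguous. The effect on the participant-rated primary outcome runs mainly through verbal delivery, telephone follow-up, adverse event recording and data entry.

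The predictability figures (60, 45 or 36 of 180) are a conditional worst case. They require enrolling staff who see the calendar, know or infer a block size that the article does not state, and know the earlier allocations. They are not an estimate of what will happen. The point is worth acting on because the weakness is avoidable at small cost.

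**What to change.** - **Scheduling.** Replace the alternate-days rule. Treat both groups on every clinic day and prevent contact with individual, non-overlapping appointments or separate rooms, with neither time slots nor rooms tied to a group. What an assessor sees after one session then says nothing about the other participants seen that day.
- **Access.** State that the treatment schedule is kept from staff who enroll and from those who collect efficacy scores.
- **Randomization.** For envelopes not yet used, replace the fixed block size with randomly varying, undisclosed sizes. Allocations already made stand.

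Adverse event recording should not be handed to the acupuncturist alone. That would place safety ascertainment entirely with the one unblinded role and exchange one bias for another.

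The cost is scheduling effort, a small risk that participants of different groups meet, and re-preparing the unused envelopes. The abstract says that recruitment began in March 2022, so the envelope change would fall within a running trial.
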